## **Study two**

### **AIM 1**

One purpose of this study is to explore the difference in the coaches' knowledge, perception of, and readiness to accept a sports injury prevention programme.

#### **Objectives**

- a. To assess if there is any difference in the knowledge of coaches towards injury prevention before and after the intervention
- b. To assess if there is any difference in perception of the soccer coaches towards injury prevention before and after intervention
- c. To assess whether the introduction of an injury prevention programme will change the readiness for injury prevention practice of soccer coaches

### **AIM 2**

A second purpose of the study is to assess the use of a warm up programme on the reduction of injuries in soccer.

#### **Objectives**

- a. To assess if there is any difference in the occurrence of injuries before and after the introduction of the injury prevention warm up programme
- b. To assess if the compliance of the injury prevention warm up programme will be associated with the reduction injuries.
- c. To determine if there is a difference in injury incidence between the intervention groups and the control group

---

 Readiness for injury prevention practice is defined as the factor that persuades coaches' engagement in activities that will influence soccer injury outcome (Siwon, 2013).

## **CHAPTER 2: METHODOLOGY**

### **2.1 RESEARCH SETTING**

The study will be conducted in Rwanda which is a land locked country situated in central Africa with a surface area of 26,338 km^2 (www.gov.rw). Rwanda is bordered to the North by Uganda, to the East by Tanzania, the Democratic Republic of Congo to the West and Burundi to the South. The population of Rwanda is 12 million with 54% of the population being under 19 years of age (EICV3). This is seen as a huge opportunity by the government of Rwanda to develop talent and the sport of soccer specifically.

The performance of Rwanda in sports in the past decade has improved because of the interest and investment of the government and the population in different aspects. In its quest to be recognized a ‘sporting’ nation the government of Rwanda tries to fairly support all the sports disciplines. There are approximately 26 national sports federations in Rwanda. Some of them have gained international recognition namely football (Soccer), paralympics, athletics, cycling, basketball and volleyball.

Currently, the soccer governing body, the Federation of Rwandan Football Association (FERWAFA) is a member of the African Football Confederation and has been affiliated with the International Federation of Football Association since January 1976 (FIFA, 2014). Each year clubs from Rwanda national teams are called upon to participate in tournaments that are organized by the continental and world governing bodies. There are 14 clubs competing in the top or first division, 19 clubs in the second division in the male category while 10 clubs participate in the female category. There are other soccer competitions organized at primary, secondary and university levels which also involve the participation of a great number of young sports men and women which will not be the focus of this study.

## **2.2 ORGANISATION OF THE STUDY**

This study is divided into two parts: one study (study 1) is a prospective cohort study that will focus on the introduction of an injury surveillance system in soccer clubs while the other part (study 2) is a randomised controlled trial that will be conducted among teams in the second division.

Both studies will be based on the Translating Research into Injury Prevention Practice framework (TRIPP) proposed by (Finch, 2006). The framework has six steps that need to be followed to build the evidence based prevention intervention (Table 1). The first two steps propose the introduction of injury surveillance and the establishment of the etiology and mechanisms of injuries. This is in line with the part one of this study which aims at establishing a system of monitoring injuries among soccer players. During this phase, additional information pertaining to the severity, burden, and treatment of injuries will be sought. Additionally, players and coaches characteristics will be assessed as well as the medical assistance available into the team.

The third step of the framework proposes the development of injury prevention measures. Literature has shown the effectiveness of a number of injury prevention strategies. The recommendation arising from recent literature is the use of an injury prevention programme called the “11+” that targets multiple factors. It is composed of 15 exercises that are divided into three parts. Part one includes running exercises at a low speed combined with active stretching and controlled partner contact. Part two is composed of six sets of exercises focusing on core and leg strength, balance and plyometrics/ agility, each with three levels of increasing difficulty. Part three is composed of running exercises at a moderate/ high speed combined with planting/ cutting movements. The exercises are designed to be incorporated into the warm up programme.

The fourth step of the framework proposes the use of scientific evaluation of the developed programme. This step corresponds to the second part of this study where the programme will be

introduced to the coaches. Additional training will be provided to the coaches of the teams in the control group pertaining to first aid and injury treatment, rehabilitation. It is believed that this study will take into consideration the knowledge and uptake of the introduced injury prevention measures. At the end of this study, injury prevention context will be identified that will help to propose a well tailored countrywide intervention as described in the stage five and six of the TRIPP framework.

Table 1: The TRIPP framework for research leading to real-world sports injury prevention

| STAGE | MODEL                                                            | Scope of the study                                                               |
|--------------|-------------------------------------------------------------------------|-----------------------------------------------------------------------------------------|
| 1            | Injury surveillance                                                     | Study 1
Injury surveillance system                                            |
| 2            | Establish etiology and mechanism of injury                              |                                                                                         |
| 3            | Develop preventive measures                                             | Study 2
Comprehensive primary, secondary and tertiary prevention intervention |
| 4            | Ideal condition / Scientific evaluation                                 |                                                                                         |
| 5            | Describe intervention context to inform implementation strategies       | Conclusions and recommendations                                                         |
| 6            | Evaluate effectiveness of preventive measures in implementation context | Dissemination                                                                           |

(Finch, 2006)

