#### **2.4.4 Participants**

Coaches and assistant coaches of the teams in the second division teams will participate in this study. The coaches have been the center of focus in recent years as the main actors in the development of soccer in Rwanda. Much training has been organized by FIFA and CAF to enhance the knowledge and practice of the coaches. Trainings pertaining to technical, tactical and physical performance of the players were provided. At the end of the training, coaches are provided certificates. Not all coaches in Rwanda are citizens and not all of them had the same training. There are therefore some differences that may arise from their coaching training, background and experience.

The coaches are required to plan and supervise training sessions to develop the fitness and the skills of the payers. Coaches are responsible for the development of the training sessions according to the demands of the competition and the period of the season. The involvement of the coach in the first division teams concerning injuries in Rwanda is relatively less compared to the coaches in the second division because the teams have medical personnel who provide assistance. They also have assistant coaches, sometimes goalkeeper coaches, and kit managers. Coaches in the second division do not have all the support needed for their work. Working with

young players, they are required to act as organizers, parents, teachers, counselors, discipliners, for them to achieve results. In the case of injuries, coaches are looked at as mature and responsible people to provide first aid, preliminary management and advice for treatment. Coaches are further responsible to allow the players to return to play after injuries.

There are 19 teams in the second division and each team has at least one head coach. The minimum number of coaches of the teams who will receive the training is 19. The assistant coaches and goalkeeper coaches of the teams in the intervention study will also participate in the study even though not all the teams have them. The total number of players participating in the in the second division league is 570.

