#### **2.4.6 Intervention**

Coaches of the teams in the second division in the intervention group will be invited to attend the training. The intervention is comprised of a five-day training divided into two parts. The first part of the training is the “11+” injury prevention programme while the second part is the training on first aid.

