##### **The “11+” injury prevention programme**

The intervention programme “The 11+” will be introduced to coaches during the training (Appendix L). Coaches will be instructed on the 15 evidence-based exercises and the promotion of Fair Play. They will be instructed on how the exercises focus on core stability, balance, dynamic stabilization, and eccentric hamstring strength and their effects on frequent injury prevention. On field practical demonstration will also be conducted. At the end of the training, each coach will receive a DVD of the exercises and the total programme instructions and a booklet for reference. Coaches will be instructed to use the training programme at least 3 times a week and at every match and will record dates and times of using the training programme. Coaches will be visited at team practice by the researcher two times a week to see if proper implementation is occurring and additional instructions will be provided where necessary. The intervention will be conducted during the preseason period, October 2015.

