## **2.4.7 Procedure**

### **2.4.7.1 Data collection**

Ethical approval, permissions and consent would be obtained during season one before conducting the study. Translation of the questionnaires into Kinyarwanda will be done before the pilot study. The translated questionnaires will be piloted among licensed five soccer coaches at school level to assess for clarity and responsiveness. A meeting will be held with them to discuss any unclear question from the translated versions and possibilities for better refining them.

During the preseason period, questionnaires assessing the knowledge of coaches regarding injury prevention will be distributed to coaches and appointment will be made for collection of the filled questionnaire. Questionnaires will be collected either by the researcher or the research assistants. Information pertaining to the availability of the medical personnel will also be obtained from the questionnaires.

Because of the changes that might take place at the end of the first season, coaches will again be invited to answer the knowledge questionnaires that will be distributed to them during the preseason period. Any other changes that will take place will also be noticed before the start of the season 2015-2016 as to the arrival of the new or change of the coaches, new teams registering into the second division league or new medical personnel arriving into the teams.

During the preseason period, July-August 2015, all the head, assistants and goalkeeper coaches of the teams in the intervention group in the second division will be invited to the training. The first part of the training will be conducted in two days where they will be taught about injury prevention in general and more specifically the importance and the use of the “11+” warm up programme. The first day will be for introduction and theoretical explanation of the conduct of the “11+” exercises while the second day will be reserved for practical demonstrations. The training will be provided by the researcher. Coaches will also be introduced to the recording of the use of the exercises while in the teams. The recording will be emphasized to ensure compliance. At the end of the training, the coaches will be provided DVDs, pamphlets and the FIFA link (where they could download the materials for free) of the exercises and will be

requested to use the “11+” as the warm up programme at least three times a week and before each match that the team will play.

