#### **2.4.9 Ethical considerations**

There is no special ethical approval, permissions or informed consent that will be required to conduct this study. Players and coaches of the teams in the intervention group will be informed that they would receive injury prevention warm up programme while the teams in the control group would continue their warm up as usual.

For coaches, there is no risk involved in participating in the study. For players, there is a risk of sustaining an injury, but the risk is minimal because the injury prevention programme and few physical tests requires players to perform physical exercises under close supervision and at minimal to moderate intensity. Because players may be found into their teams, verbal information will be provided to them where the researcher will read them the information sheet. They will therefore be requested to sign the consent forms indicating their agreement to participate in the study.

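### The protocol does not settle which arm's coaches receive first aid training, so the between-group injury comparison may test a combined package rather than the 11+ warm-up

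*Combined protocol and SAP*

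**What the plan says.** Five places describe who is trained.

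- **Section 2.2** assigns training to the control arm: "Additional training will be provided to the coaches of the teams in the control group pertaining to first aid and injury treatment, rehabilitation". Table 1 in the same section labels Study 2 "Comprehensive primary, secondary and tertiary prevention intervention".
- **Section 2.4.4** counts one head coach for each of the 19 second-division teams and concludes: "The minimum number of coaches of the teams who will receive the training is 19".
- **Section 2.4.6** states: "Coaches of the teams in the second division in the intervention group will be invited to attend the training". It gives this training two parts: the 11+ comes first, "while the second part is the training on first aid".
- **Section 2.4.7.1** again invites the intervention-group coaches. It then says that coaches will be taught first aid, without naming an arm.
- **Section 2.4.9** says of the controls only that "the teams in the control group would continue their warm up as usual".

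Aim 2 (Sections 1.3 and 2.4.2) is about the use of a warm-up programme to reduce injuries. The sample size in Section 2.4.4.3 ties its 20% reduction to the 11+.

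Delivery details also differ. The 11+ part of Section 2.4.6 says "The intervention will be conducted during the preseason period, October 2015", while Section 2.4.7.1 says "During the preseason period, July-August 2015, all the head, assistants and goalkeeper coaches of the teams in the intervention group" will be invited. Section 2.4.6 gives the training five days; the component descriptions give two days for the 11+ and two for first aid.

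**The concern.** A two-arm trial estimates the effect of whatever differs between the arms. If the intervention coaches learn both the 11+ and first aid while the controls carry on as usual, a difference in injury incidence belongs to the package, and Aim 2 as worded would credit the warm-up with all of it. If both arms receive the same first aid training, the difference can be read as the effect of the 11+.

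The protocol itself gives reasons not to treat first aid training as inert. Section 2.4.6 includes guidance on taking an injured player off the field. Section 2.4.4 says second-division coaches give first aid and decide on return to play. Section 1.1 says that resuming play without proper care can aggravate injuries, and it cites a trial of coach-controlled return to play with fewer re-injuries. The glossary grades severity by days absent and defines recurrence from the return to full participation. An effect on severity or re-injury is therefore plausible.

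If the point stays open, the comparison could be delivered differently from what was intended, or described only once the results are known.

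**Working it through.** **Step 1: the trained head count.** Inputs: 19 teams with at least one head coach each (Section 2.4.4); groups of nine or ten teams (Section 2.4.4.4).

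- Both arms: 19 teams × 1 head coach = 19. This reproduces the plan's figure.
- One arm: 9 × 1 = 9, or 10 × 1 = 10.

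A single arm could reach 19 only by counting assistant or goalkeeper coaches. Section 2.4.4 says not every team has them, so they cannot support a minimum. The figure of 19 therefore implies training in both arms.

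**Step 2: the statements side by side.**

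| Section | Intervention coaches | Control coaches |
|---|---|---|
| 2.2 | 11+ introduced to coaches, arm not named | First aid, treatment, rehabilitation |
| 2.4.4 | Trained (19 needs both arms) | Trained (19 needs both arms) |
| 2.4.6 | 11+ and first aid | Not mentioned |
| 2.4.7.1 | 11+; first aid follows, arm not named | Not mentioned |
| 2.4.9 | Warm-up programme | Usual warm-up; first aid not mentioned |

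**Step 3: the contrast under each workable reading.**

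- Following 2.4.6 and 2.4.7.1, with controls on usual practice: (11+ and first aid) minus (usual practice) = effect of the package. Here 2.2 is wrong, and 19 should be 9 or 10.
- Following 2.2 and 2.4.4 as well: (11+ and first aid) minus (first aid-type training) = broadly the effect of the 11+. Here 19 is right. The word broadly is needed because 2.2 adds treatment and rehabilitation for controls, which the first aid content in 2.4.6 does not list.

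**Step 4: which objectives depend on this.** Aim 1, objectives a to c, concern change in coaches before and after the intervention. Aim 2, objective a, is before and after, and objective b concerns compliance with the 11+. Objective c is the comparison of injury incidence between groups, and its meaning changes with the reading.

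**Step 5: delivery.** Length: 2 + 2 = 4 days against 5, so one day is unexplained. Date: October is two months after August and three after July, so the stated dates differ by two to three calendar months.

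**The case against.** The strongest reply is that this is loose drafting rather than contradiction. No section says that only intervention coaches are trained. Sections 2.4.6 and 2.4.7.1 say whom one training invites, and a usual warm-up for controls does not exclude first aid. One reading fits most of the text: the 11+ and first aid for the intervention arm, first aid-type training for controls, 19 teams' coaches trained in all. On that reading Aim 2 roughly isolates the 11+. Table 1 also openly presents Study 2 as a multi-level intervention. Finally, Figure 3 and Appendices J and M, which might set out each arm's content or the daily schedule, were not in the text examined.

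Much of this stands, and it is why the second reading in the working is a live one. It does not settle the matter. The favourable reading relies on a control-arm training that appears in one sentence of 2.2 and has no date, trainer or length in 2.4.6 or 2.4.7.1. Table 1's label sits alongside an aim and a sample size worded for the warm-up alone. A figure or appendix could explain the intent, but the conflicting sentences would remain.

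A reader might infer more than the documents support:

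- **That every Study Two outcome is affected.** Most objectives are before-and-after comparisons or concern compliance.
- **That a between-arm test of first aid knowledge is lost.** None is planned in the visible text; Section 2.4.8 compares coaches' knowledge between divisions.
- **That first aid goes to controls alone, so its effect is subtracted from that of the 11+.** This means setting aside 2.4.6, which makes first aid part of the intervention.
- **That all 19 teams receive the full training, leaving no contrast.** Section 2.4.9 keeps controls on their usual warm-up.

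**Conclusion.** The concern holds for the between-group injury comparison. The protocol supports two different contrasts, the combined package against usual practice or broadly the 11+ alone, and it words the aim and the sample size for the second without establishing that the first is excluded. The number of head coaches trained is 9 or 10 on one reading and 19 on the other.

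The effect on the injury result cannot be sized, because the documents give no estimate of what first aid training does to injury incidence. Any such effect would be wholly inside the contrast on the first reading and broadly balanced out on the second, to the extent that the two arms' first aid content matches.

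The conclusion assumes that the minimum of 19 counts head coaches, as its context indicates, and that nothing in Figure 3 or Appendices J and M overrides the main text. The conflicts of date and length are real but secondary: they do not bear on which arm is trained.

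**What to change.** Replace the scattered descriptions in Sections 2.2, 2.4.4, 2.4.6, 2.4.7.1 and 2.4.9 with one statement of what each arm's coaches receive, and cite it wherever training is mentioned. Then align the claim with it:

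- **If first aid training differs between arms**, reword Aim 2 and its between-group conclusion as the effect of the combined training package, which agrees with Table 1. Word the sample-size rationale to match.
- **If both arms receive the same first aid training**, keep Aim 2 as the effect of the 11+. State that the content is the same, and say whether the treatment and rehabilitation topics in 2.2 apply to one arm or both.
- **The figure of 19** should change only if a single arm is trained; otherwise add a line saying that it counts both arms.

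Separately, reconcile the training date (October against July-August 2015) and length (five days against two plus two).

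The cost is protocol wording. If the package reading is the intended one, the conclusion about the warm-up becomes narrower. This should be settled before any coach is trained, since afterwards the contrast can be described but not chosen.

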## **2.3 STUDY ONE: INTRODUCTION OF INJURY SURVEILLANCE SYSTEM**

### **2.3.1 Aim**

The purpose of the study is to establish an injury surveillance system in soccer teams in Rwanda.

### **2.3.2 Objectives**

- a. To determine the difference in etiology, nature, severity and location of injuries between first and second division soccer players
- b. To assess whether there is any relationship between injury pattern and players' age, playing position and division of play.
- c. To assess if there is any difference in injury pattern according to training and match exposure
- d. To describe the availability of the medical support into the teams

